#### Exclusion criteria

Parents will be excluded if, during the initial intake interview, they i) have insufficient English language skills to complete the interview; ii) demonstrate very high levels of distress, anxiety, and/or depression on the Emotion Thermometers Tool (that is, scores ≥ 7) [39] and endorse serious suicidal intent; iii) endorse symptoms of psychosis or substance abuse; or iv) have a child who is currently on active treatment, has relapsed, or is in palliative care. Any participant who is excluded will be provided with appropriate referral options, if desired.

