## Methods/Design

The Cascade study is a multi-site, randomised controlled trial (RCT) to assess the feasibility and efficacy of a new, online, CBT-based intervention for the parents or legal guardians (hereafter referred to as ‘parents’) of young cancer survivors (see Additional file 1 for a list of participating centres and ethical bodies). Parents of children under 16 years of age who have completed cancer treatment with curative intent and achieved remission in the past 12 months will be recruited and randomised to one of three arms: i) Cascade, ii) a peer-support group (PSG) control, or iii) a 6-month waitlist control. Informed consent will be obtained from all participants. The 1- to 12-month timeframe was chosen to maximise the benefit to participants, by delivering the coping skills intervention early in their child’s survivorship period. The intervention, named ‘CASCAdE’ (*C*ope, *A*dapt, *S*urvive: Life after *CA*nc*E*r), is delivered live, in real-time, to groups of 3 to 5 parents by a psychologist (hereafter referred to as ‘facilitator’) in four, weekly online sessions. Participants also receive an online introductory session with the facilitator before the group commences and a ‘booster’ session one month after the end of the group to facilitate consolidation of skills.

Cascade will be compared with the active PSG control in order to assess the relative benefits of peer-based support and contact with any additional psychological benefits gained from learning structured, skills-based coping strategies. ‘Peer-support’ type models of support are ubiquitous in community settings, yet few PSGs have been rigorously evaluated [36]. Consequently, little evidence exists to support the appropriateness of PSGs alone in addressing distress in parents of children with cancer. The PSG arm holds constant the amount of treatment contact, human interaction variables (such as facilitator warmth and interaction between participants), as well as controlling for participants’ expectations of receiving some form of treatment [37].

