**Table 1 Tab1:** **Assessment schedule for the cascade study**

**Measure**	**Intake**	**Q1** ^**a**^	**During intervention** ^**b**^	**Q2** ^**c**^	**Q3** ^**d**^	**Q4** ^**e**^	**Q5** ^**f**^
Psychosocial Adjustment to Illness Scale-Interview form (PAIS)	**X**	**-**	**-**	**-**	**-**	**-**	**-**
Demographic data	**-**	**X**	**-**	**-**	**-**	**-**	**-**
Treatment Intensity Scale	**-**	**X**	**-**	**-**	**-**	**-**	**-**
Medical and general functioning^g^	**-**	**X**	**-**	**X**	**X**	**X**	**X**
Paediatric Quality of Life Inventory (PedsQL) Generic Core Scale^h^	**-**	**X**	**-**	**X**	**X**	**X**	**X**
Paediatric Quality of Life Inventory (Family Impact Module)	**-**	**X**	**-**	**X**	**X**	**X**	**X**
EQ-5D-5 L	**-**	**X**	**-**	**X**	**X**	**X**	**X**
Parenting Self Agency Measure (Revised)	**-**	**X**	**-**	**X**	**X**	**X**	**X**
CBT skills use	**-**	**X**	**-**	**X**	**X**	**X**	**X**
PROMIS parent mental health and functioning short-form items^i^	**-**	**X**	**-**	**X**	**X**	**X**	**X**
California Psychotherapy Alliance Scale - Group (CALPAS-G)	**-**	**-**	**-**	**X**	**-**	**-**	**X**
Intervention satisfaction items	**-**	**-**	**-**	**X**	**-**	**-**	**X**
Emotion Thermometers Tool	**X**	**-**	**X**	**-**	**-**	**-**	**-**
Homework Compliance Scale	**-**	**-**	**X**	**-**	**-**	**-**	**-**
Working Alliance Inventory - Short	**-**	**-**	**X**	**-**	**-**	**-**	**-**

^**a**^Q1 = Baseline; ^**b**^During intervention = weekly prior to intervention sessions 2 to 4; ^**c**^Q2 = post-intervention.

^**d**^Q3 = Week 5 follow-up, ^e^Q4 = 6 month follow-up; ^f^Q5 = after waitlist participants have completed the intervention.

^g^Including other psychological support received; ^h^Parent proxy and child self-report; ^i^Items assess parent depression and anxiety symptoms.

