### Participants

This study will recruit 120 parents (approximately 40 in each arm). This sample size will allow medium-to-large differences in parent QoL to be detected with a power of 80% at a two-tailed significance level of 0.05 (assuming Cohen’s d = 0.65 as the difference in change from time 1 to time 2 for any pair of groups, standardised on the pooled within-group standard deviation). This effect size is clinically significant [38]. It is anticipated that approximately 375 parents will need to be approached to achieve a final sample of 120 participants (assuming a 40% response rate and 20% attrition rate).

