#### Safety monitoring

This trial includes safety monitoring and management procedures at multiple project stages (see Figure 2). The intake interview carefully screens for acutely suicidal/severely depressed participants. Participants will also be regularly screened for mood deterioration during intervention participation when they complete the weekly Emotion Thermometers Tool [39] (see *Assessments*). Any deterioration in mood of more than three points on the tool will trigger protocols involving the facilitator contacting the participant to discuss their emotional state and a meeting between the researchers to develop a management plan (which may include contacting their nominated health professional, with the participant’s consent).

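### Exclusion criterion ii, read literally, excludes serious suicidal intent only when an Emotion Thermometers score is also 7 or more

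*Protocol article*

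**What the plan says.** Under Exclusion criteria, the protocol article lists four grounds, assessed at the intake interview. The second applies to parents who "demonstrate very high levels of distress, anxiety, and/or depression on the Emotion Thermometers Tool" (a score of 7 or more) "and endorse serious suicidal intent". The other three concern insufficient English, psychosis or substance abuse, and a child who is on active treatment, has relapsed or is in palliative care. The Inclusion criteria do not mention suicidality. The Exclusion criteria section closes with a promise of referral: "Any participant who is excluded will be provided with appropriate referral options, if desired".

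Under Safety monitoring, the article says: "The intake interview carefully screens for acutely suicidal/severely depressed participants". That sentence ties suicidality to no score and does not say what follows when the screen is positive. The section refers to Figure 2 for the procedures at each stage; the figure is not available here.

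Eligible parents are randomised to Cascade, to the peer-support group or to "a 6-month waitlist control", with "approximately 40 in each arm" (section Participants).

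**The concern.** An exclusion for suicidal risk would normally stand on its own, because the risk does not depend on a second instrument reaching a cut-off. Here it does depend on one. Criterion iii shows the contrast: endorsing psychosis or substance abuse excludes with no score attached, whereas endorsing serious suicidal intent does not.

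What is at stake is participant safety. If the criterion is applied as written, a parent with serious intent and moderate scores may enter the trial, possibly on the waitlist. The article promises referral options only on exclusion. It does not rule out referral for others, but it does not guarantee it. Power, the mixed-model analysis and randomisation balance are not materially touched.

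**Working it through.** No figure in the plan depends on this, so the check is one of logic, followed by two small sums on allocation and cost.

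**The rule as written.** Criterion ii = (any of the three scores is 7 or more) AND (serious suicidal intent). Its outcome in the four possible cases:

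- Score 7 or more, intent: excluded.
- Score 7 or more, no intent: eligible.
- All scores below 7, intent: eligible.
- All scores below 7, no intent: eligible.

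Two of the four cases involve serious intent, and the rule excludes one of those two. The third case is the gap. Criteria i, iii and iv do not reach it.

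**The rule with intent standing alone.** Both intent cases are excluded and both no-intent cases stay eligible. Exactly one case of four changes, the third.

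**Is the joined wording a slip of the reader?** The same clause uses a both-or-either connective for distress, anxiety and depression, and criterion iii uses a plain alternative. The text thus distinguishes its connectives, and the literal reading of criterion ii is that both parts are required.

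**Set beside Safety monitoring.** That section names acutely suicidal and severely depressed parents as the targets of the intake screen, with no threshold. A screen aimed at acute suicidality sits awkwardly with a criterion that ignores intent below a score of 7. But screening is not the same as excluding: a parent could be identified and then managed or referred while still eligible. Both passages can be true together.

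**Allocation of a parent in the gap.** With about 40 of 120 parents per arm, the chance of the waitlist is 40/120 = 1/3, and of an active arm 80/120 = 2/3. These chances are conditional on such a parent existing and being randomised.

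**Would later monitoring notice?** The stated trigger is a deterioration of more than three points on the same thermometers during the intervention. Table 1 schedules the tool at intake and then, in its footnote, "During intervention = weekly prior to intervention sessions 2 to 4". No thermometer reading is scheduled for a waitlisted parent during the wait. Waitlisted parents do complete the PROMIS depression and anxiety items and the EQ-5D-5L at Q1 to Q4, but the visible text gives no alert rule for those questionnaires.

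**Cost in recruitment.** Expected opt-ins are 375 × 0.40 = 150, and 150 × 0.80 = 120 retained, which reproduces the planned target. One more exclusion gives 149 × 0.80 = 119.2, a loss of 0.8 of a retained parent, or 1/150 = 0.67% of opt-ins. Inviting 1/0.40 = 2.5 more parents restores it.

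**The case against.** The strongest reply is that the article does not show the whole safety procedure. Figure 2 is missing from the text at hand and may set out what happens at intake to any parent who endorses intent. An intake script or risk procedure is also something a journal article commonly leaves to the full protocol. This stands in part: it limits what can be said about how such a parent would actually be handled. It does not repair the criterion, which is printed in full. If Figure 2 excludes on intent alone, criterion ii should be aligned with it.

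A second reply is that the joined wording has a purpose: it keeps highly distressed but non-suicidal parents in the trial. That stands. Distress severity on the same tool is a balancing factor in the randomisation, and these parents should remain eligible. The purpose does not require intent to depend on a score.

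A third reply is that the gap can be filled only if intent is asked of everyone. The article does not say how, or of whom, intent is elicited; Table 1 lists only the PAIS and the thermometers at intake. This also stands, and it means that rewording alone may not be enough.

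Finally, there are safeguards. Every parent names a trusted health professional, and active-arm parents meet the facilitator live each week. These reduce the consequence but do not settle who may be enrolled.

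A reader might go further and infer that Exclusion criteria and Safety monitoring contradict each other. The documents do not support that, because Safety monitoring states no exclusion rule. Nor do they support the inference that suicidal parents would go unnoticed on the waitlist, since Figure 2 is not visible and questionnaires continue there.

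**Conclusion.** The point holds as a defect of eligibility wording with a safety consequence. Read literally, criterion ii leaves one of the two serious-intent cases outside every listed exclusion. That fits poorly with the intake screen's stated aim, without contradicting it.

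The size is one case of four in the rule, not a number of parents. The documents give no frequency for serious intent with all scores below 7, so none is claimed. The conclusion assumes the literal reading of the criterion and that staff follow it. How such a parent would be handled in practice remains open. The correction should be made because the possible harm is grave and the change is small, but nothing in the trial's power, analysis or interpretation turns on it.

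**What to change.** Reword criterion ii so that parents are excluded if they endorse serious suicidal intent, whatever their Emotion Thermometers score. State that intent is asked of every parent at intake regardless of score; without that step the new wording may not reach the parents it is meant for. Leave parents scoring 7 or more without suicidal intent eligible, as now. Check that Figure 2 says the same.

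Parents excluded under the new wording then fall under the existing referral promise. The cost is one line of eligibility text, a question put to all parents at intake if it is not already, and an amendment at the approving hospitals listed under Study integrity. A very few parents may become ineligible, each offset by two or three extra invitations. The Trial status section describes recruitment as ongoing and expected to finish by June 2016, so an amendment could still protect later recruitment blocks.

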#### Access considerations

To participate in the study internet access and a suitable computer set-up is required. This includes access to a computer/tablet that has a microphone and web-camera and can be used privately and uninterrupted once per week for four weeks. Participants will be loaned an insured tablet and/or web-camera and internet access USB device if needed (the costs of which are covered by Cascade’s project grant).

#### Participant recruitment

Potential parent participants will be mailed an invitation package comprising a personalised invitation letter from the Head of Oncology or their child’s treating oncologist at their child’s treating centre, a consent form, and an opt-in card, as well as a separate child assent form. The research officer will contact all parents who opt in to assess their technology needs and, if a loan is required, request that participants sign and return a written contract agreeing to use the equipment solely for study purposes.

Recruitment will occur in 5 × 12 week blocks, such that approximately 75 parents will be invited 4 weeks prior to Week 1 of each block. Using our expected response and attrition rates, it is envisaged that five iterations (that is, 5 × 12 week blocks), each attracting approximately 30 parent opt-ins, will be required to achieve the target sample. This means that five mail outs (approximately 75 parents at a time) will occur during 2014/5. All fully consented participants will be telephoned by the research officer 2 weeks prior to Week 1 to administer the Psychosocial Adjustment to Illness Scale Interview (PAIS) [40]. Participants will also complete the first online questionnaire at this time. See Figure 1 for the study flowchart.

**Figure 1 Fig1:**
[figure not shown]
Cascade study flowchart.

### Randomisation

Participants will be randomised to one of the three arms using a flexible biased urn method of randomisation, which adapts to the degree of imbalance between groups in a dynamic manner over the trial [41]. This method is superior to standard stratification in balancing groups across multiple covariates [42,43], whilst also being a suitable method when groups remain small [41,44,45]. The groups will be balanced across two factors: i) severity of distress as measured by the Emotion Thermometers Tool [39] and ii) degree of rural/remoteness as assessed by the Accessibility/Remoteness Index of Australia [46]. An independent researcher will electronically randomise participants to treatment group.

### Interventions

#### Cascade

Cascade is guided by the family systems illness model [47]. This evidence-based framework conceptualises resilience in families as a multifaceted process involving the interaction between negative sequelae (stressors) and positive responses (coping strategies), with a key role for family members’ appraisal of the stressor in determining adaptive coping responses. Cascade derives its proposed core mechanisms of change from CBT and addresses both positive and negative outcomes after cancer. CBT may be particularly effective in improving QoL in carers of cancer patients if it targets communication and problem solving skills (both addressed in Cascade) [48]. Each Cascade module applies CBT techniques to the key domains of concern identified in our previous research [4,49] (see Table 2). Our strengths-based approach recognises that families are resilient and competent [31], which means that Cascade builds on psychological strengths while mitigating negative symptoms in the broadest possible group.

**Table 2 Tab2:** **Cascade intervention content**

	**Module title and description**	**Relevant cognitive-behavioural therapy strategies**
**Module 1**	*‘What just happened to us?!’*	Peer discussion to normalise range of typical parent experiences.
	*Processing the cancer experience and getting back to some form of ‘normal’.*	Behavioural activation to improve mood, fatigue, and activity levels.
**Module 2**	*‘How has cancer changed the way I think?’*	Peer discussion to normalise increase in frequency and intensity of worries after cancer.
	*Managing upsetting thoughts and worries about cancer and everything else.*	Psycho-education about common unhelpful thinking styles
		Cognitive challenging.
**Module 3**	*‘Out of your head and back into life’*	Peer discussion to normalise existential concerns and highly distressing worries (for example, about child’s possible death).
	*Mindfulness and acceptance-based strategies for easing the struggle with ‘bigger’ existential concerns and emotional pain.*	Practical problem solving strategies for problems with logical solution(s).
		Cognitive strategies for disengaging from patterns of unhelpful thinking (for example, attention training, mindfulness exercises).
**Module 4**	*‘Looking forward’*	Peer discussion to normalise changes to relationships and feelings of isolation after the cancer experience.
	*Skills for fostering meaningful relationships, accessing social support and living a rich and fulfilling life after cancer.*	Supportive discussion and problem-solving strategies to stimulate support seeking from family and network.
		Assertive, effective communication skills strategies.
**Booster**	*Individual ‘catch-up’ session with each parent one month after the end of the group.*	Assist participant to identify challenging situations in the past month according to cognitive-behavioural model, and review helpful coping skills.
		Review goal from the start of the program - discuss what has helped and what remains challenging in this area.

Participants randomised to Cascade will participate in four, live, weekly, 90-minute sessions facilitated by a psychologist. Each group will comprise a psychologist and three to five participants with mixed cancer experiences (such as the age of their child and their child’s type of cancer). Participants also receive a purposely developed workbook, outlining the content of each session, providing additional examples and suggesting ‘homework’ activities to facilitate skill development. Additional files 2, 3 and 4 show details of the workbook content and graphic design.

Sessions will be delivered through WebEx (Cisco WebEx, USA). WebEx requires a computer with standard browser, a high-speed internet connection, and a webcam. WebEx is a secure, password-protected video-conferencing program that allows up to six participants to be seen on the screen simultaneously, similar to group Skype™. Participants will receive a reminder text message on their cellular phone 24 hours before their session, which will also serve as their reminder to complete the Emotion Thermometers Tool [39] and homework compliance scale (see *Assessments*).

#### Peer-support group (active control)

The PSG control is delivered in an identical manner to Cascade (via WebEx, up to five participants per group), with the same frequency of contact (four weekly 90-minute sessions) and availability of peer-based group discussion. The PSG is delivered by the same facilitator as Cascade (see *Treatment fidelity* for further discussion). Like Cascade, it also involves supportive counselling to normalise the range of parent experiences and provides parents an opportunity to give and receive emotional/practical support. During each session, parents are encouraged to exchange information about a nominated topic (matched to those addressed in Cascade for example, ‘relationships and social support’). The key distinction between Cascade and the PSG is that the PSG does not include directive, structured teaching of specific, CBT-based coping skills. The PSG in this trial will adhere to best practice guidelines [50] and is manualised to ensure standardisation across all sessions.

### Procedures

Following recruitment, participants will complete a telephone intake interview with a Cascade research officer to further screen for participant eligibility, orient participants to the study procedures, ascertain any technical needs, and complete the PAIS [40].

Participants will then be randomly allocated to a study arm. During Weeks 1 to 4 of each 12-week block, those allocated to Cascade and the PSG will participate in their allocated intervention. Waitlist controls will be assessed at the same time points as the intervention groups, and will be randomly allocated to either Cascade or PSG during weeks 26 to 30. The waitlist group will also complete a final questionnaire (Q5) after participating in the intervention. Parents will be sent links via email to complete the questionnaires (see *Data management and analysis*) and will be encouraged to supervise their child/ren while they complete the questionnaires, if desired.

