**Methods/Design:**

The ‘Cascade’ (*C*ope, *A*dapt, *S*urvive: Life after *C**A*nc*E*r) study is a three-arm randomised controlled trial to evaluate the feasibility and efficacy of a new intervention to improve the quality of life of parents of young cancer survivors. Cascade will be compared to a peer-support group control and a 6-month waitlist control. Parents (n = 120) whose child (under 16 years of age) has completed cancer treatment in the past 1 to 12 months will be recruited from hospitals across Australia. Those randomised to receive Cascade will participate in four, weekly, 90-minute online group sessions led live by a psychologist. Cascade involves peer discussion on cognitive-behavioural coping skills, including behavioural activation, thought challenging, mindfulness and acceptance, communication and assertiveness skills training, problem-solving and goal-setting. Participants randomised to peer support will receive four, weekly, 90-minute, live, sessions of non-directive peer support. Participants will complete measures at baseline, directly post-intervention, one month post-intervention, and 6 months post-intervention. The primary outcome will be parents’ quality of life. Secondary outcomes include parent depression, anxiety, parenting self-agency, and the quality of life of children in the family. The child cancer survivor and all siblings aged 7 to 15 years will be invited to complete self-report quality of life measures covering physical, emotional, social and school-related domains.

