#### Inclusion criteria

Eligible parents will meet the following inclusion criteria: i) have a child under 16 years of age who has completed cancer treatment with curative intent in the past 12 months; ii) be able to give informed consent; iii) be able to read English; iv) be able to provide the contact details of a trusted health professional, such as their local general practitioner; and v) be able to access the Internet in a private location (see also *Access considerations* below). Children will be eligible if they are aged 7 to 15 years and, in the opinion of the parent, are capable of reading at a Grade Two level. In this study, we are interested in parents of young cancer survivors aged less than 16 years, and so we matched siblings to this age range. Child participants will require parental consent.

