#### Child psychosocial functioning

The Paediatric Quality of Life Inventory (PedsQL) Generic Core [62] parent proxy-report scale will be used to assess the cancer survivor’s quality of life in physical, emotional, social, and school-related domains of functioning. In a recent review of QoL measures for children, the PedsQL emerged as a feasible and valid tool that is widely used in cancer and chronic disease [63]. All participating children (the child survivor and/or any siblings) will also complete a child self-report version of the scale.

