### Data management and analysis

All measures (excluding the PAIS telephone interview) will be administered online through Key Survey (WorldAPP, Braintree, MA, USA) at all time points, unless paper versions are requested by participants. Key Survey enables participants’ data to be securely downloaded to files amenable to statistical analysis using the Statistical Package for the Social Sciences, version 18.0 (SPSS, Inc., Chicago, IL, USA).

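### Encouraging the treated parent to supervise the child's questionnaires puts the child self-report, a secondary outcome, at avoidable risk of bias

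*Protocol article*

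**What the plan says.** All quotations are from the protocol article.

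- **Procedures:** "Parents will be sent links via email to complete the questionnaires", and parents "will be encouraged to supervise their child/ren while they complete the questionnaires, if desired". The wording is the same for all three arms and all time points.
- **Data management and analysis:** "All measures (excluding the PAIS telephone interview) will be administered online through Key Survey", with paper versions on request.
- **Child psychosocial functioning:** for the survivor, the PedsQL Generic Core "parent proxy-report scale will be used to assess the cancer survivor’s quality of life". In addition, "All participating children (the child survivor and/or any siblings) will also complete a child self-report version of the scale". No proxy rating is described for siblings.
- **Abstract, Methods/Design:** "Secondary outcomes include parent depression, anxiety, parenting self-agency, and the quality of life of children in the family".
- **Inclusion criteria:** children are aged 7 to 15 and must, in the parent's opinion, be able to read: they "are capable of reading at a Grade Two level".
- **Study integrity and Treatment fidelity:** assessments are described as blind, and the person blinded is the research officer.

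**The concern.** A child self-report is collected alongside a parent proxy to obtain a view that does not pass through the parent. Here the parent has three roles: randomised participant, proxy rater of the survivor, and invited supervisor of the self-report. The instruction as printed does not separate technical help from watching or shaping the answers.

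Two things are at stake. First, if parents in one arm come to influence answers differently from parents in another, the between-arm contrast in child quality of life includes that influence as well as any real effect. Second, even with no difference between arms, answers drawn towards the parent's view make the self-report less useful as a second informant. This matters because the Discussion presents the assessment of possible impact on children as part of what makes the programme unique.

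**Working it through.** **1. Is there a figure in the plan to reproduce?** Not for this outcome. The sample size in the Participants section concerns parent quality of life. With d = 0.65, two-sided 0.05 and 80% power, n per arm = 2 × (1.96 + 0.84)² / 0.65² ≈ 37.1, which rounds up to 38 and agrees with the stated figure of about 40. No target effect, standard deviation or number of children is given for the child outcome.

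**2. Does the stated blinding cover the situation?** No. The research officer is blind, but the forms are completed online through links sent to the parent. The person who may be beside the child is the treated parent. That parents know their allocation is inferred from the design. It is unavoidable for group versus a six-month wait. It is less certain for Cascade versus peer support, because the Methods/Design section says the peer-support arm controls for expectation of treatment.

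**3. When would supervision bias the contrast?** Let p be the share of children supervised and δ the mean shift in a supervised child's score, in SD units. For arms A and B at T1 and T2, the bias in the difference in change is

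(p_A2·δ_A2 − p_A1·δ_A1) − (p_B2·δ_B2 − p_B1·δ_B1).

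- Participant recruitment places the first questionnaire around the telephone interview, two weeks before Week 1. Procedures places allocation after that interview. Baseline therefore appears to precede allocation, so p_A1·δ_A1 and p_B1·δ_B1 are equal in expectation.
- The bias then reduces to p_A2·δ_A2 − p_B2·δ_B2.
- If p and δ stay the same, or change equally in both arms, the bias is zero. It arises only if supervision or its influence differs by arm after allocation.

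This assumes that the child outcome is analysed as change from T1, as Statistical analyses describes for quality of life.

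**4. Illustration only.** The inputs are assumptions, and zero is possible.

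- Suppose the same share p is supervised in two arms but the shift differs by Δ. The bias is p × Δ. With p = 0.3 and Δ = 0.2 it is 0.06 SD; with p = 0.7 and Δ = 0.4 it is 0.28 SD. Because Δ is itself an assumed arm difference, this shows scale and does not establish that a bias exists.
- With no true effect and a spurious shift of b SD, n independent children per arm and s = b / √(2/n), the two-sided false-positive rate is Φ(s − 1.96) + Φ(−s − 1.96):

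| Children per arm | b = 0 | b = 0.1 | b = 0.2 | b = 0.3 |
|---|---|---|---|---|
| 20 | 5.0% | 6.2% | 9.7% | 15.8% |
| 40 | 5.0% | 7.3% | 14.5% | 26.9% |

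**5. Is supervision of answers needed?** Eligible children must already read at the stated level. That is only the parent's judgement, so help with reading remains reasonable for the youngest. It does not call for overseeing the choice of answers.

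**The case against.** Supervision is optional and the invitation is the same in every arm. Supervising is not the same as helping to answer: when a link goes to a parent's email and the child may be seven, an adult nearby is ordinary. Baseline forms are completed under the same invitation, apparently before allocation, so a stable effect of presence largely cancels in change from T1. A journal article may also leave detailed instructions to parents, or an item on presence, to the full protocol or study materials, so their absence here is no fault.

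Most of this stands. It limits the point to a risk and confines it to the sentence as printed. It does not remove the point. Identical wording does not ensure identical behaviour once some parents have been through a programme and others are waiting, and the loss of an independent informant needs no arm difference at all. Any record kept elsewhere would not undo the encouragement.

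A reader might go further and infer that the child outcome is biased, that communication training leads Cascade parents to alter answers, or that agreement between proxy and self-report becomes worthless. The documents do not support these. They give no supervision rate, show no such mechanism, and do not plan to use that agreement as corroboration. Nor are the items described as being about family matters: the scale covers physical, emotional, social and school functioning.

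**Conclusion.** The point holds as an avoidable risk of bias in a named secondary outcome. The plan encourages the treated parent, who is also the survivor's proxy rater, to supervise the one child measure meant to be independent of that parent, and the research officer's blinding does not offset this. Distortion of the between-arm change depends on supervision or its influence diverging by arm after allocation, most plausibly for group versus waitlist and less clearly for Cascade versus peer support. The weakening of the self-report as a second informant depends only on supervision pulling answers towards the parent's view.

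The size cannot be derived from the documents, and the figures above rest wholly on assumed inputs. A reader might be tempted to set 0.28 SD against d = 0.65 and call it roughly 40% of the target effect. That comparison is not valid, because 0.65 is a standardised change in parent quality of life and no target exists for children. The primary outcome and the sample size are unaffected.

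**What to change.** Replace the encouragement in Procedures with one instruction, identical in all arms and at all time points: a parent may help with log-in, technical problems, and reading or explaining a word, but the child chooses the answers without prompting or discussion. This need not forbid a parent from being in the room or seeing the form, which would be debatable for minors.

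Add one item to each child questionnaire, at every time point, asking whether a parent was present or helped with answers. Report it by arm and time point, and add a sensitivity analysis of the child self-report by that record. Interpret that analysis cautiously: help is recorded after randomisation and is probably commoner among the youngest, so setting assisted forms aside could itself introduce selection.

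The cost is a reworded email instruction, one extra online item and possibly a few more incomplete forms among the youngest children. As recruitment was still open when the article appeared, starting the new wording with a new recruitment block would keep each family under one instruction throughout, at the price of leaving earlier families under the existing one.
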